##### Drug consumption

2.4.2.12

The type and dose of medication (medication prescribed due to current medical history or rescue medication) taken during the study period will be checked through a questionnaire during each visit. For treatments other than the medication taken such as the injections, the number of the treatments will be recorded.

### Timeline of participants

2.5

The timeline of the study is shown in Table 1.

### Sample size estimation

2.6

To estimate the number of study subjects, the results of the unpublished pilot study was used. Based on the pilot study, the effect size of MSAT for patients with neck pain is 0.55. When estimating the number of samples while using the *t* test as the primary analysis, the result showed that 106 subjects in total (53 per group) will be required. However, since the analysis of covariance is the primary analysis in this study, using the correlation coefficient of the mean difference between the baseline value and primary endpoint calculated through the pilot study, 0.24, the corrected number of samples was determined to be 100. Considering a dropout rate of 20% and recruitment from 4 institutions, a total of 128 subjects (64 subjects per group) were calculated as the number of samples required to conduct the clinical trial.

The calculation was performed based on the assumption level of significance at α=0.05 (2-sided test) and 80% of the power of the test with type 2 error (β) at 0.2. G∗Power 3.1.9.7 was used to estimate the sample size.

### Recruitment

2.7

Subjects will be recruited using online advertising media and promotional posters, inside, and outside the study institutions.

### Randomization and allocation concealment

2.8

In this study, a balanced block randomization method will be used. Each study institution will be set as strata, and 2, 4, or 6 will be used at random for the block size. Randomization will be performed by the statistical analysis manager using SAS Version 9.4 (SAS institute. Inc., Cary, NC) to create a random table with the same probability of each individual being selected. When a random table is assigned for each institution, it will be divided into a control group and an experimental group according to the randomization code, and 64 subjects will be assigned to each of the groups.

The generated randomization results will be sealed in envelopes, delivered to each institution, and managed in a cabinet with a double lock. Randomization will be conducted only on subjects who have voluntarily provided written consent after a sufficient explanation of the clinical trial. The randomization envelope will be opened in front of the subject, the subject will be assigned to the randomized group, and the envelope will be stored separately in a cabinet with a double lock. Randomization results cannot be viewed in advance and cannot be changed after assignment

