### Blinding

2.9

Due to the nature of the intervention in this study, it is impossible to blind the physicians and patients. However, in this study, the statistical analysis manager and the outcome assessor will be blinded to secure objectivity and reduce the bias as much as possible. Outcome assessment will be performed in a separate space before the treatment is performed by an assessor, who will not participate in the treatment and does not know the patient's group assignment, and has received standardized training for the data collection procedures.

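### The statistical analysis manager both creates the randomisation lists and is declared blinded, so the claimed analyst blinding is not secured as written

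*Protocol article*

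**What the plan says.** Three places in the protocol article bear on this point.

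- **Section 2.8, Randomization and allocation concealment.** "Randomization will be performed by the statistical analysis manager using SAS Version 9.4". The resulting table is assigned to each institution and divided into control and experimental arms according to the randomisation code. The section continues: "The generated randomization results will be sealed in envelopes, delivered to each institution, and managed in a cabinet with a double lock". Allocation is stratified by site with randomly varied block sizes ("2, 4, or 6 will be used at random for the block size").
- **Section 2.9, Blinding.** Because of the intervention, "it is impossible to blind the physicians and patients". As compensation, "the statistical analysis manager and the outcome assessor will be blinded to secure objectivity and reduce the bias as much as possible".
- **Discussion.** The article repeats that physicians and patients cannot be blinded, and relies on blinded outcome assessors and statistical analysts to keep the trial objective.

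No section states that list generation and analysis are done by different people, or that the analyst works from masked codes.

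**The concern.** The person who generates a randomisation list ordinarily has the allocation sequence. If the same person later chooses models, handles missing data and settles analysis populations, the analysis is not blinded, whatever the blinding section says.

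The point matters more here than in a double-blind trial. Patients and physicians know the arm, and the primary outcome, VAS on movement, is marked by the patient. A separate assessor cannot remove the patient's own knowledge. Blinding of the analyst is one of the remaining protections, and the article relies on it twice.

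The plan also leaves some room for analytic judgement. Section 2.11 runs two primary analyses side by side (intention-to-treat among those treated at least once, and per-protocol). It also allows costs and effects to be extrapolated beyond follow-up by regression or decision modelling if that is judged necessary. Such decisions are better made by someone who cannot see the arms.

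**Working it through.** **The contradiction.** The plan gives no figure on this point, so the check is a comparison of the text.

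1. Section 2.8 names the statistical analysis manager as the one who performs the randomisation and creates the table.
2. Section 2.8 says that the generated results go into the sealed envelopes. What the generator produces is therefore, on its natural reading, the allocation itself.
3. Section 2.9 names the same role as blinded. The title is identical, so this is not a matter of two similarly named posts.
4. Does another section separate the two duties? Section 2.10 conceals the cleaned and locked e-CRF data from all investigators except the one in charge of data management. It concerns outcome data and does not mention the randomisation list. Section 2.13 (monitoring) does not address the list either.
5. Statements 1 and 3 can both be true only if some unstated arrangement keeps the generator from knowing the arms. The article gives none.

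**A side check: does the block scheme add a second problem?** Section 2.8 gives the block sizes, the stratification by site and the opening of envelopes at the site. Two inputs are assumed: 128/4 = 32 patients per site, and sizes 2, 4 and 6 equally likely.

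Take a guesser who always names the arm that is behind in the current block and tosses a coin when the arms are level. In a block of size m, exactly m/2 allocations move the arms back towards balance, and all of these are guessed correctly. Each allocation made from a level position adds one half. So

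expected correct guesses = m/2 + ½ × (expected number of level positions before an allocation).

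| Block size | Expected level positions | Expected correct | Share |
|---|---|---|---|
| 2 | 1 | 1 + 0.5 = 1.5 | 75.0% |
| 4 | 1 + 4/6 = 1.667 | 2 + 0.833 = 2.833 | 70.8% |
| 6 | 1 + 12/20 + 12/20 = 2.2 | 3 + 1.1 = 4.1 | 68.3% |

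- Sizes 2, 4 and 6: (1.5 + 2.833 + 4.1)/12 = 70.3%.
- Sizes 4 and 6: (2.833 + 4.1)/10 = 69.3%.

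This guesser is credited with knowing where each block begins. A simulated guesser who knows the set of sizes and the site's past allocations, but not the block boundaries, and who guesses optimally, gives:

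| Sizes | Correct guesses | Known with certainty in advance |
|---|---|---|
| 2 only (fixed) | 75.0% | 50% |
| 2, 4, 6 (as planned) | 69.8% | about 4.0% |
| 4, 6 | 68.9% | about 5.6% |

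Dropping size 2 lowers correct guessing by about 1 percentage point (69.8 − 68.9 = 0.9) and raises the share of certain allocations by about 1.6 points (5.6 − 4.0).

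**The case against.** **The article is condensed.** Masked codes, a second statistician or an unblinding procedure may be set out in the full protocol, an operating procedure or an analysis plan that is not shown. The division of the table into arms is written in the passive, so it is not stated who links codes to treatments. This stands in part. It rules out the stronger conclusion, which a reader might draw, that analyst blinding does not exist in this trial. It does not remove the point, which is not about missing detail. The article makes two positive statements about one role and they conflict, so its wording needs correcting whatever another document says.

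**Analyst blinding matters little here.** The main bias risk is that unblinded patients report their own pain, and no analyst blinding addresses that. Section 2.9 also provides a separate blinded assessor. Section 2.11 fixes the ANCOVA with baseline as covariate, multiple imputation with 20 datasets and a last-observation-carried-forward sensitivity analysis, and it rules out interim analysis. This stands and lowers the severity. Some discretion remains, as noted above, and the authors themselves present analyst blinding as a safeguard.

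**The opposite temptation: block size 2.** A reader might infer that including size 2 lets site staff work out the next allocation. Within a block, the second allocation is opposite to the first with probability (1 + 2/3 + 3/5)/3 = 76%, but that figure requires knowing that a new block has just begun. The sizes vary at random, which mostly hides the boundaries, and the envelopes are sealed and kept under double lock. Guessing at about 70% is a general feature of small permuted blocks in an open-label, site-stratified trial. It is hardly changed by removing size 2, and the share of certain allocations would rise. The documents do not support treating the block sizes as an error.

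**Conclusion.** The role contradiction stands. Sections 2.8 and 2.9 cannot both be taken at face value, and the Discussion relies on the one that is not secured. The conclusion rests on the article's text alone and on the premise that whoever generates a list can see it. It does not assert that the analyst will in fact be unblinded.

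No effect on the estimate, type I error or power can be computed from the documents, and none is claimed. The severity is moderate: this should be fixed before the analysis, but it does not undermine the design, since the main analysis is largely prespecified and the larger bias risk lies in unblinded self-report. No finding is made against the block sizes. That part rests on the two assumptions of 32 patients per site and equally likely sizes.

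**What to change.** - Assign generation and custody of the site lists to an existing staff member with no role in the analysis. The same SAS program can be used.
- Give the statistical analysis manager only masked group codes until the analysis is final.
- Reword Section 2.8 to name the list generator's role, and Section 2.9 to say how the analyst is kept blinded, so that the two agree with each other and with the Discussion.
- If the manager has already generated the lists and the analysis cannot be given to someone else, withdraw the analyst-blinding claim from Section 2.9 and the Discussion, and keep only the claim about the outcome assessor.

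The cost is one reassigned task and a few sentences of text. Sample size, visits, treatment and the block scheme stay as they are.

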### Blinding

2.9

Due to the nature of the intervention in this study, it is impossible to blind the physicians and patients. However, in this study, the statistical analysis manager and the outcome assessor will be blinded to secure objectivity and reduce the bias as much as possible. Outcome assessment will be performed in a separate space before the treatment is performed by an assessor, who will not participate in the treatment and does not know the patient's group assignment, and has received standardized training for the data collection procedures.

### Data collection and management

2.10

In this study, an electronic Case Report Form (e-CRF), based on the internet-based clinical research management systems operated by the Korea Disease Control and Prevention Agency, will be used. Before commencing the study, standard operating procedures (SOP) will be developed, and training will be provided for investigators in each of the institutions about the detailed SOP and e-CRF writing guidelines. Double data entry verification will be conducted to ensure the accuracy of the data entered into the e-CRF and the investigators of each institution will be responsible for the accuracy of the entered data. Data entered in the e-CRF will be cleaned, locked, and concealed from all investigators, except for the investigator in charge of data management.

### Statistical analysis

2.11

This study will be a randomized controlled study that analyzes the pain intensity scale, functional scale, quality of life, and costs data results of patients who meet the selection criteria.

The primary analyses will be the intention-to-treat analysis, which evaluates those who have received treatment at least once, and the per-protocol analysis, which evaluates only those who have successfully completed the clinical study, excluding those who have been dropped out; the 2 analyses will be performed concurrently.

For processing the missing values, multiple imputations using the Markov Chain Monte Carlo method will be used as the primary method, and 20 imputed datasets will be generated. In addition, the last observation carried forward method will be used for the sensitivity analysis.

The sociodemographic characteristics and treatment expectancy of the subjects will be evaluated for each of the groups. Continuous variables will be represented as mean (standard deviation) or median (quartiles), and categorical variables will be represented as a frequency (%).

The effectiveness endpoint of this clinical trial will be the difference in the amount of change between baseline and each time point by the group for the continuous outcomes (NRS, VAS, NDI, NPQ, EQ-5D-5L, and SF-12). Analysis of Covariance will be performed using the baseline values of each variable as covariates and the group as a fixed factor.

For the sensitivity analysis, datasets without the imputed values will be used to analyze the degree of change from the baseline. The mixed-effects repeated measures analysis will be performed for the primary and secondary outcomes at all time points. The time variable will be included as a categorical variable and the interaction terms of group and time will be included at each time point to evaluate the difference in the effectiveness of MSAT.

To compare the total amount of difference between 2 groups for each outcome within the treatment period (2 weeks) and the entire study period (8 weeks), the areas under the curve (AUC) within each period after randomization will be calculated. The difference in AUC between the 2 groups will be compared using the independent student *t* test.

Survival analysis for VAS of neck pain will be performed. At each time point, the patient ratio will be comparatively analyzed for each time point when the neck pain VAS falls below half of the baseline. A Kaplan–Meier survival analysis will be used to estimate the time until less than half of the neck pain recovery occurs after randomization, and the differences between groups will be compared using a log-rank test. Also, the Cox model will be used to estimate the hazard ratio.

All statistical analyses will be performed using the SAS version 9.4 statistical package (SAS Institute, Cary, NC) with the significance level set to *P* < .05. In addition, the analysis will be performed after the end of the study (when all patients follow-ups have been completed) and interim analysis will not be allowed.

In addition, this study aims to investigate the cost-effectiveness between MSAT and acupuncture treatment through an economic evaluation. The primary economic endpoint will be the incremental cost-effectiveness ratios of cost per Quality Adjusted Life Years (QALY) of the MSAT group against the acupuncture treatment group. The analysis period is the entire study period including the intervention period and follow-up period, and if estimation for the subsequent period is required, the costs and effectiveness after the follow-up period will be estimated by extrapolation through a regression model or a secondary analysis with decision modeling analysis.

Medical costs will be calculated based on the number of treatments and the unit cost. For the unit cost, data on health insurance costs, institutional cost data, and patient answers will be used. The quality of life estimation for the QALY calculation, the quality of life derived by EQ-5D-5L will be used as the main endpoint, and EQ-VAS, and SF-6D will be used for the sensitivity analysis. The AUC method will be used for calculation. The units for the costs will be unified in Korean currency (won) as of 2020 and a 5% discount rate will be applied based on the guidelines for the economic evaluation of the Health Insurance Review and Assessment Service and represented in US dollars using the published exchange rate.

Considering the characteristics of non-parametric data, 95% CI of the incremental cost-effectiveness ratios of cost per QALY will be estimated using the bootstrapping technique. In addition, the probability that of MSAT being cost-effective will be examined using the cost-effectiveness acceptability curves graph according to the degree of willingness to pay. All analyses will be made for costs through the healthcare system and social perspectives.

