#### Exclusion criteria

2.2.2

1)Participants diagnosed with a serious disease that can cause pain (e.g., Migration of cancer reaching to spine, fracture of the spine, and dislocation of the spine)2)Progressive neurologic deficits or severe neurologic deficits3)Participants diagnosed with a soft tissue disease that can cause pain (Cancer, fibromyalgia, rheumatoid arthritis, or goat)4)Presence of chronic diseases (e.g., Cardiovascular disease, kidney disease, dementia, diabetic neuropathy, or epilepsy)5)Participants on steroids, immunosuppressants, or psychotropic medication6)Participants who are inadequate or unsafe for acupuncture (e.g., Hemorrhagic disease, severe diabetes, or taking the anticoagulant drug)7)Participants that took NSAIDs or underwent acupuncture treatment within the last 3 days8)Participants that had undergone cervical surgery within the last 3 months9)Participants that had a traffic accident within a month10)Pregnant women or women who planned to conceive11)Participants that had participated in another clinical trial within 1 month or planned to participle in other trials within 6 months of the enrollment12)Participants that could not provide informed consent13)Participants that found it difficult to participate in the trial according to the investigator's decision

The patient may be dropped in clinical trials in the case of an unexpected risk or serious adverse events are occurred. The PI would make the final decision if to drop the patient.

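### Section 2.11 ranks two analysis sets as primary without saying which decides, and the one called intention-to-treat leaves out randomised patients who never start treatment

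*Protocol article*

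**What the plan says.** All from the protocol article.

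- **Two primary analyses (section 2.11):** "The primary analyses will be the intention-to-treat analysis, which evaluates those who have received treatment at least once, and the per-protocol analysis". Their relation is only that "the 2 analyses will be performed concurrently".
- **First set (2.11):** the intention-to-treat analysis is the one "which evaluates those who have received treatment at least once".
- **Second set (2.11):** the per-protocol analysis "evaluates only those who have successfully completed the clinical study, excluding those who have been dropped out".
- **Missing data (2.11):** "multiple imputations using the Markov Chain Monte Carlo method will be used as the primary method", with 20 imputed datasets. The text does not tie this to either set.
- **Significance level (2.11):** P < .05, with no allocation between the two analyses.
- **Knowledge of allocation (2.8 and 2.9):** "The randomization envelope will be opened in front of the subject", and neither patients nor physicians can be blinded.
- **Primary outcome (2.4.1):** VAS on movement, baseline to week 3. Follow-up continues to week 8 (2.1).
- **Sample size (2.6):** one comparison, effect size 0.55, two-sided alpha 0.05, 80% power, ANCOVA as the primary model, 20% dropout, 128 patients.

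**The concern.** Two separate problems meet in one sentence of section 2.11.

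First, two analyses share the primary rank and nothing says which carries the conclusion. A reader cannot tell whether a claim needs the first, either or both. Those three rules have different error rates and power, and a choice made after the results are known cannot be shown to be independent of them.

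Second, neither set contains everyone randomised. The intention-to-treat set requires at least one treatment. Where treatment is blinded, failing to start is usually unrelated to the arm. Here the patient sees the allocation when the envelope is opened, so someone disappointed with the arm can leave before the first session and vanish from every planned analysis set. The per-protocol set goes further and removes all dropouts. Read literally, completing the study means reaching week 8, so a patient with a valid week-3 VAS who is lost afterwards is excluded from a co-primary analysis of the week-3 outcome.

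This is not a detail left to an unseen analysis plan. The article states two primary analyses and defines the term intention-to-treat in a way that conflicts with its meaning.

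**Working it through.** **Step 1. Reproduce the plan's sample size (section 2.6).** A two-sample t test with d = 0.55, two-sided alpha 0.05 and power 0.80 needs 53 per group, 106 in total (noncentral t; power at 53 is 0.801). The ANCOVA correction is 106 × (1 − 0.24²) = 106 × 0.9424 = 99.9, so 100. Dropout: 100 / 0.8 = 125, or 63 per arm (126). The stated 128 is 32 per site over four sites. The plan's figure reproduces, and it is built on one test.

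**Step 2. Type I error if either analysis may carry the claim.** Treat the two test statistics as bivariate normal with correlation r and critical value 1.96. Then P(either) = 1 − P(|Z1| < 1.96 and |Z2| < 1.96). If completers are a random fraction f of the larger set and that set has an observed week-3 value for everyone, r = √f.

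| Completers f | r | P(either significant) |
|---|---|---|
| 0.95 | 0.975 | 0.060 |
| 0.90 | 0.949 | 0.065 |
| 0.80 (the plan's dropout) | 0.894 | 0.071 |

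With week-3 values of dropouts imputed, the two tests share more information and r is higher. A null simulation (64 per arm, 20% missing at random, 20 imputations, ANCOVA on baseline with correlation 0.24) gave:

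| Imputation uses | r | P(either significant) |
|---|---|---|
| Arm and baseline only | 0.994 | 0.055 |
| Plus an interim VAS correlated 0.5 with week 3 (assumed) | 0.97 | 0.061 |
| Plus an interim VAS correlated 0.7 with week 3 (assumed) | 0.95 | 0.065 |

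At the plan's 20% dropout the range is therefore about 5.5% (values imputed from little) to 7.1% (values observed).

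**Step 3. Power if both must succeed.** The ANCOVA effect is 0.55 / √(1 − 0.24²) = 0.567. With n per arm the expected statistic is 0.567 × √(n/2): 3.20 for 64 and 2.86 for 51 (64 × 0.8, rounded). With r = √(51/64) = 0.893 and the normal approximation:

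- 64 per arm alone: 0.89
- 51 completers per arm alone: 0.82
- both significant: 0.80 (0.802 with 51 completers per arm, 0.795 with 50)

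The 0.89 assumes week-3 values are observed for all 64. If dropouts' values are imputed, the larger set's power is lower and the gap to the both-must-win rule narrows.

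**Step 4. Size of the never-treated exclusion (illustrative).** The article gives no count. Assume 5 of 64 in one arm leave when the envelope is opened and differ in prognosis by 0.5 SD. The arm mean moves by 5/64 × 0.5 = 0.039 SD, which is 0.039 / 0.55 = 7% of the planned effect.

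**The case against.** - **The text implies that the larger set decides.** Multiple imputation makes most sense there, since the completer set has dropped the patients who would need it. That is a fair inference, but the article does not say so, and its wording gives both sets equal rank.
- **The error inflation needs an either-wins rule that the document never states.** This stands. The 5.5% to 7.1% describes one of the readings left open, and its upper end needs observed week-3 values for dropouts, which the dropout allowance in 2.6 does not suggest.
- **Never-treated patients are probably few, and imputing them from baseline and arm barely moves the estimate.** Also largely right. Even the assumed 5 of 64 gives a small shift, and imputation cannot recover a prognostic difference that baseline does not explain. Continued follow-up could, which is why the fix includes it.
- **Defining per-protocol by adherence is commonly left to the analysis plan.** Accepted; no finding is made of it.

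Three stronger readings are tempting and should not be drawn:

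- *The primary outcome is undefined.* Section 2.11 applies its effectiveness endpoint to change "between baseline and each time point" on several scales, which is loose. But the abstract and sections 2.3.3, 2.4.1 and 2.6 together fix VAS on movement, week 3, ANCOVA and one sized comparison, and 2.4.2 lists the other scales as secondary.
- *The PI may remove patients at will.* Section 2.2.2 says "The PI would make the final decision if to drop the patient", but the sentence before it limits this to unexpected risk or serious adverse events. A patient dropped after one session also stays in the larger set.
- *Requiring both analyses pushes power below the planned 80%.* Step 3 gives about 80%, because 128 already allows for dropout.

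**Conclusion.** The point holds. Section 2.11 names two primary analyses with no deciding rule, and neither set keeps all randomised patients, in a trial where allocation is known before treatment starts. Under an either-wins rule two-sided type I error would be about 5.5% to 7.1% instead of 5%. Under a both-must-win rule power is about 80% instead of about 89%.

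These figures treat completers as a random subset of the larger set. The 89% and the 7.1% further assume observed week-3 values in the larger set, while the lower error figures rest on the simulated imputation. Bias from arm-related dropout would come on top and is not quantified.

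A reader might infer that randomisation no longer protects the comparison. The documents do not support that: they give no number of never-treated patients, and the illustrative shift is 0.04 SD. The main weakness is that the deciding analysis is not fixed before the data are seen.

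**What to change.** In section 2.11, and in any analysis plan that follows it:

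1. Name one confirmatory analysis: VAS on movement, change from baseline to week 3, ANCOVA with baseline as covariate, all randomised patients in the arm assigned, with the multiple imputation already planned.
2. Keep collecting the week-3 VAS from patients who do not start or who stop study treatment.
3. State that the per-protocol analysis is supportive.
4. If a treated-at-least-once set is kept, call it modified intention-to-treat and give it a sensitivity role.

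The cost is mostly wording, plus the effort of obtaining week-3 VAS from patients who leave treatment. N stays 128, and the single test keeps two-sided alpha at 5%. The downside is that a few never-treated patients will need imputed values, which may slightly dilute the estimate. The change should be made before any outcome data are seen by arm.
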